#### **9.4. Study Drug Preparation**

NKTT120 is a liquid formulation and reconstitution is not required. In preparation for use as an IV infusion, NKTT120 will be diluted in sterile normal saline (NS). Preparation of NKTT120 for IV infusion should be performed by the clinical study pharmacist using the Pharmacy Manual.

#### **9.5. Administration**

Study drug should be administered according to the study specific instructions detailed in the Pharmacy Manual.

Should the subject experience any adverse event during the infusion, the infusion rate should be slowed or stopped according to the discretion of the investigator until the symptom has resolved or the Subject stabilized (see Pharmacy Manual for details). If restarted, the infusion should be slowed according to the discretion of the investigator (see Pharmacy Manual for details).

Should CRS of any type be observed in subjects in any cohort, premedication with acetaminophen (1000 mg), histamine 2 receptor antagonists (diphenhydramine, 50 mg) and corticosteroids may be initiated prior to dosing of subsequent subjects to lessen severity of CRS.

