To further address the possibility of CRS in response to treatment with NKTT120 in humans, the effect of NKTT120 on cytokine release *in vitro* in human whole blood was evaluated. Incubation of whole blood in the presence or absence of 20  $\mu$ g/ml of NKTT120 (a concentration higher than the predicted exposure following a dose of 1 mg/kg) for 24 hours did not result in a cytokine response in any of 4 donor samples. In contrast, incubation with an anti-CD3 mAb resulted in substantial elevation of several cytokines (IFN $\gamma$ , IL-4, IL-10, IL-17, TNF $\alpha$ , IL-2, IL-5, IL-8, IL-1RA and MIP-1) in at least two of the four donor samples. These data suggest that in contrast to the activation of the variable T cell receptor by anti CD3, NKTT120-mediated binding to the invariant receptor of iNKT cells has no measurable cytokine-inducing effect in an *in vitro* human whole blood setting.

Although the available *in vitro* and *in vivo* data suggests that the risk of CRS following the administration of NKTT120 is low, the theoretical risk remains and subjects will be closely monitored for signs of CRS in the clinical study. Stopping the infusion and administration of a histamine blocker is usually sufficient to manage reactions for most subjects who experience mild or moderate infusion reactions. Once symptoms subside, usually within 30 minutes, the infusion can often be restarted cautiously at the investigator's discretion, at half the initial rate and titrated as tolerated, without further symptoms (Kosits, 2000).

Delayed infusion reactions are uncommon but may occur days after the infusion. Symptoms associated with delayed infusion reactions include arthralgias, skin rash, leukocytic vasculitis, urticaria, myalgias, and fever. Symptoms may be self-limiting or may improve with administration of corticosteroids (Weber, 2004; Barbaud, 2011).

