#### **4.6.1.1. Allergic Reactions and Anaphylaxis**

In contrast to symptoms associated with CRS, true allergic-type reactions typically are more severe when subjects are re-challenged. In this first in human phase I trial, all subjects will be observed for acute allergic-type reactions for at least 6 hours after the infusion of NKTT120. The clinical site and clinical staff must be prepared to handle allergic reactions, including anaphylaxis

---

and no subject should be discharged from the clinical site if they are unstable or have any of the signs or symptoms of a delayed allergic reaction.

Delayed allergic reactions could occur, after the subject leaves the clinic; therefore, subjects will be instructed in the signs and symptoms of a delayed reaction (including swelling, tenderness, and/or itching at the site of infusion, rhinorrhea, sneezing, coughing, shortness of breath, nausea, dizziness, wheezing, rash or faintness, pruritus, urticaria, scratchy throat, throat or tongue swelling) and will be instructed to contact the clinical site, or seek medical attention, immediately if they notice any of these signs and symptoms after leaving the clinical site.

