## **18.2. Management of infusion reactions**

Should CRS of any type be observed in subjects in any cohort, premedication with acetaminophen (1000 mg), histamine 2 receptor antagonists (diphenhydramine, 50mg) and corticosteroids may be initiated prior to dosing of subsequent subjects to lessen severity of CRS.

Should the subject experience any local discomfort or adverse event during the infusion, the infusion should be stopped until the discomfort has resolved or the subject stabilized. Stopping the infusion and administration a histamine blocker is usually sufficient to manage reactions for most subjects who experience mild or moderate infusion reactions.

Once symptoms subside, usually within 30 minutes, the infusion can often be restarted cautiously at the investigator's discretion, at half the rate and titrated as tolerated without further symptoms

If restarted, the infusion should be slowed to deliver 2.5 mL/min.

**If there is no further reaction**, continue at 50% rate of infusion **or** resume original rate of infusion.

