***The infusion should not be restarted if the subject's symptoms have not resolved within one hour.***

***The infusion should not be restarted if the subject experienced a severe reaction.***

### **18.3. World Medical Association Declaration of Helsinki**

#### Ethical Principles for Medical Research Involving Human Subjects

Adopted by the 18th WMA General Assembly, Helsinki, Finland, June 1964, and amended by the:

29th WMA General Assembly, Tokyo, Japan, October 1975  
35th WMA General Assembly, Venice, Italy, October 1983  
41st WMA General Assembly, Hong Kong, September 1989  
48th WMA General Assembly, Somerset West, Republic of South Africa, October 1996  
52nd WMA General Assembly, Edinburgh, Scotland, October 2000  
53rd WMA General Assembly, Washington 2002 (Note of Clarification on paragraph 29 added)  
55th WMA General Assembly, Tokyo 2004 (Note of Clarification on Paragraph 30 added)  
59th WMA General Assembly, Seoul, October 2008

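### Section 9.5 lets the investigator slow the infusion for a reaction where section 18.2 says stop, omits the 18.2 limits on restarting, and does not refer to 18.2

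*Protocol*

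**What the plan says.** Section 9.5 (Administration) sends the site to the Pharmacy Manual for giving the drug. For an adverse event while the drug is running, it says "the infusion rate should be slowed or stopped according to the discretion of the investigator until the symptom has resolved" (or the subject is stable). On resumption it says "If restarted, the infusion should be slowed according to the discretion of the investigator". Both sentences refer to the Pharmacy Manual for details. The section gives no restart rate and no condition under which restarting is ruled out.

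Section 18.2 (Management of infusion reactions) says "Should the subject experience any local discomfort or adverse event during the infusion, the infusion should be stopped until the discomfort has resolved" (again, or the subject is stable). It allows a cautious restart at the investigator's discretion at half the rate, and then specifies "If restarted, the infusion should be slowed to deliver 2.5 mL/min". If no further reaction follows, the infusion may continue at 50% or return to the original rate. The section closes with two bars. One applies if "symptoms have not resolved within one hour". The other reads "The infusion should not be restarted if the subject experienced a severe reaction".

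Section 4.6.1, discussing cytokine release, describes stopping for mild or moderate reactions and then often restarting "at half the initial rate and titrated as tolerated". Section 4.6.1.1 notes that "true allergic-type reactions typically are more severe when subjects are re-challenged".

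**The concern.** The two sections deal with one clinical situation and also carry nearly the same sentence on premedication after cytokine release. They do not give the same instruction, and the section on giving the drug is the more permissive of the two.

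Section 4.5 states that this is the first study of NKTT120 in humans. Section 6.1 keeps each subject in the clinic for at least 6 hours so that infusion reactions, cytokine release and allergic reactions can be seen. What the site does when such a reaction begins is therefore a central safety instruction. A site that follows 9.5 could continue at a lower rate through a reaction, or resume after a severe one, and find nothing in 9.5 against it. The limits on renewed exposure appear only in an appendix that 9.5 does not mention.

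There is a secondary point about consistency. The grade 3 cytokine criterion quoted in section 6.6.1 depends partly on how symptoms respond to a brief interruption of the infusion and on whether they recur. Grade 3 events go to the Safety Review Committee as possible dose-limiting toxicities. In a multi-center study with three to six subjects per cohort, reactions should be handled alike at every site.

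**Working it through.** The check is a comparison of text; the plan has no figure of its own to reproduce.

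**Step 1: is the trigger the same?** Section 9.5 applies to any adverse event while the drug is being infused. Section 18.2 applies to any such event and adds local discomfort. Every event covered by 9.5 is therefore also covered by 18.2.

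**Step 2: are the instructions the same?**

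| Point | Section 9.5 | Section 18.2 | Relation |
|---|---|---|---|
| Immediate action | Slow or stop, at discretion | Stop | Conflict: slowing satisfies 9.5 and departs from 18.2 |
| Restart rate | Slower, at discretion | 2.5 mL/min, described as half the rate | 9.5 is looser; both can be met by following 18.2 |
| Severe reaction | Silent | No restart | Omitted from 9.5 |
| Symptoms persisting beyond one hour | Silent | No restart | Omitted from 9.5 |

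**Step 3: does anything reconcile them?** Section 9.5 cites the Pharmacy Manual three times and never cites 18.2. Section 18.2 does not cite 9.5. Apart from its own heading, 18.2 appears only in the table of contents. No sentence sets an order of precedence.

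**Step 4: which section is out of line?** The description in 4.6.1 (stop, then half the initial rate) agrees with 18.2, so 9.5 is the outlier.

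**Step 5: is the 2.5 mL/min rate consistent with half the rate?** Section 6.2.2 gives an infusion time of 10 minutes. If 2.5 mL/min is half the initial rate, then:

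- initial rate = 2 × 2.5 mL/min = 5 mL/min
- implied volume = 5 mL/min × 10 min = 50 mL

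The protocol does not state the volume; preparation and administration are left to the Pharmacy Manual. The 50 mL figure is thus an inference to confirm. It is not a further conflict, and the finding does not depend on it.

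**The case against.** The strongest reply is that only the first row of the table is a true conflict. The two bars on restarting are in the protocol, in a section devoted to infusion reactions. An administration section need not repeat them, and a site that restarted after a severe reaction would still be departing from 18.2. The restart rates are compatible. Section 18.2 has discretion of its own: whether to restart, how to titrate, and whether to return to the original rate. The Pharmacy Manual, which is not available here, may repeat the 18.2 limits in full. The text in 4.6.1 describes usual practice and is not a trial instruction, and the remark in 4.6.1.1 on re-challenge is general and does not specifically address resuming an interrupted infusion. Few subjects may be affected, since the text matters only if an event occurs during a 10-minute infusion.

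Much of this is fair. The bars are omitted from 9.5, not contradicted by it, and the supporting passages give context without binding the site. The planned enrolment of about 30 is no measure of the risk.

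The conflict over slowing or stopping remains, and an unseen manual cannot remove a disagreement inside the protocol. The discretion in 18.2 extends neither to slowing in place of stopping nor to the two bars. A careful reader of the whole protocol could satisfy both sections by following 18.2, but 9.5 does not send the site there.

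**Conclusion.** The concern holds: section 9.5 is wrong as written and should be fixed. Measured by the text, there is one direct conflict, one looser instruction and two omitted safety limits, with no cross-reference and no rule of precedence. It bears on subject safety and on uniform handling of reactions across sites. It changes no endpoint, sample size, escalation probability or analysis.

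The conclusion rests on the protocol text alone. It does not assume that the Pharmacy Manual lacks the limits, and it makes no estimate of how often a reaction will occur during infusion, because the documents give no figure for that.

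**What to change.** Replace the sentences in 9.5 on slowing, stopping and restarting with: *If any adverse event occurs during the infusion, stop the infusion and follow section 18.2, which governs stopping and restarting.*

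In 18.2, keep the instruction to stop and both bars on restarting. State the restart rate as half the initial rate, or confirm that 2.5 mL/min equals it for the volume in the Pharmacy Manual. Check that the Pharmacy Manual gives the same instructions.

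The cost is an edit to 9.5, one line in 18.2 and a check of the manual. No subjects, visits or procedures are added. The downside is slightly less freedom for the investigator with mild events. If the sponsor wants to keep slowing as an option for these, it should say so in 18.2, define which events qualify, and have 9.5 refer to that text.

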#### **9.6. Study Drug Accountability**

Drug accountability records will be maintained for all clinical trial supplies. The study center will complete the drug accountability records to document the receipt, dispensing and return or destruction of study drug (NKTT120 vials) throughout the study. NKTT personnel or representatives will monitor the completeness and accuracy of all accountability records throughout the course of the study. NKTT or designee will verify product accountability against site documentation and all study product, used and unused. Unused materials will be destroyed at the site according to the site's procedure or returned after reconciliation by the study monitor according to the written instructions provided by NKTT.

#### **9.7. Study Drug Handling and Disposal**

##### **10.7.1 Handling Instructions**

NKTT120 is provided as a 1 mL sterile solution in a single use, glass vial at a nominal concentration of 10 mg/mL and is formulated as described in the section above (Section 9.1).

NKTT120 must be stored upright and frozen at temperature between -20° C (-14 and -26 °C or 7 and 15 °F). It must be stored in the original carton until time of use.

##### **10.7.2 Disposal Instructions**

At the end of the study any unused drug will be destroyed at the site according to the site's standard operating procedures. Study drug will not be returned unless instructed to do so by NKTT.

If the study drug is to be destroyed at the site, it is the investigator's responsibility to ensure that arrangements have been made for the disposal and procedures for proper destruction have been

established according to applicable regulations, and institutional procedures. Appropriate records of the destruction must be documented and maintained by the site.

The unused or damaged study drug may only be destroyed after inspection and reconciliation by the responsible NKTT CRA or representative. A copy of the destruction record will be kept in the study files at the site and copies will be maintained in the study master files.

If study drug (NKTT120) is to be returned to the NKTT, it must be accompanied by the appropriate documentation and be clearly identified by the protocol number, study site number and Principal Investigator name. Returned drug should be in the original container. Detailed instructions and contact information are provided in the Pharmacy Manual.

## **10. PHARMACOKINETIC ASSESSMENTS**

### **10.1. Blood Sample Collection**

Blood for PK sampling will be collected at the following time points (see [Table 3](#)): day 0 pre-dosing and post-dose 15 minutes, 30 minutes, 1 hour, 3 hours and 6 hours after end of infusion; day 1, day 2, day 3, day 7, day 14; and at each monthly visit, including the EOS visit. Times of start of infusion and end of infusion will be recorded and the actual time each PK sample was drawn will be recorded, using a 24 hour clock. Samples will be processed in the serum, stored frozen at -70°C. Samples will be analyzed after completion of each cohort. Sites that cannot store samples at -70°C will store samples at -20°C and will ship samples to the Blood Center of Wisconsin within 14 days of collection.

### **10.2. Sample Analysis**

Serum samples for PK analysis will be shipped to the Blood Center of Wisconsin laboratory for analysis. Samples will be analyzed using a validated ELISA for detection of NKTT120 in human serum. Refer to the laboratory manual for shipping details.

## 11. ASSESSMENT OF SAFETY

### 11.1. Safety Parameters

All adverse Events of Interest (EOI, below) that could be dose-limiting toxicities will be reviewed immediately by the SRC to determine if they constitute a DLT. All serious adverse events at any time will be reviewed by the SRC so that the SRC can make recommendations to the Sponsor regarding dosing cohorts. All safety data, including adverse events and laboratory abnormalities, will also be reviewed by the SRC periodically in order to assist the sponsor in evaluating potential safety signals during the follow-up until iNKT cells recover.

**Event of interest (EOI) Criteria:** an EOI is defined only for adverse events that occur within 2 weeks of dosing (with the exception of any acute vaso-occlusive episode). Any adverse event grade 3 or higher on NCI CTCAE version 4.03 will be considered an EOI. Additionally, the following study and disease-specific toxicities will be considered an EOI.

- **Cytopenias:** Defined as CTCAE version 4.03 Grade 3 or 4 leukopenia, neutropenia, lymphopenia or thrombocytopenia.
- Specific grade 3 definitions in CTCAE version 4.03 are:
  - Leukopenia: <2000 cells/cubic milliliter
  - Neutropenia: <1000 cells/cubic milliliter
  - Lymphopenia: <500 cells/cubic milliliter
  - Thrombocytopenia: < 50/microliter
- **Infections:** Defined as CTCAE version 4.03 grade 3 or 4. Specific infections are detailed in the CTCAE. Broadly the definition is a severe infection that requires IV antibiotic, antifungal or antiviral therapy, or otherwise severe and medically significant, but not necessarily life-threatening.
- **Cytokine storm syndrome:** Defined as CTCAE version 4.03 grade 3 or 4. The grade 3 definition reads: Prolonged (eg, not rapidly responsive to symptomatic medication and/or brief interruption of infusion); recurrence of symptoms following initial improvement; hospitalization indicated for clinical sequelae (eg, renal impairment or pulmonary infiltrates)
- **Sickle cell-specific dose limiting toxicities:**
  - Hemolysis:
  - Anemia: >25% decrease in hemoglobin from baseline or  $\leq 5.0$  g/dL
  - Lactate dehydrogenase increase 3-fold from baseline
  - Reticulocyte count increase 3-fold from baseline
  - AST increase 3-fold from baseline
  - Total bilirubin increase 3-fold from baseline

- **Acute vaso-occlusive episode:** within the 6-hour monitoring window following infusion, an increase in pain over baseline ( $\geq 4$  points on a 10 point pain scale) in the extremities, chest, abdomen or head lasting for at least 2 hours that could not be explained except by sickle cell disease.
- **Increased pain in the extremities, chest, abdomen or head lasting for at least 2 hours:** Within 72 hours following infusion, a provider encounter (clinic, ED or hospital), requiring opioid administration and could not be explained except by sickle cell disease.

#### 11.1.1. Demographic/Medical History

Medical history will be obtained at screening pre-run-in to determine if there are any clinically significant diseases or medical problems, other than SCD, that would affect the subject's ability to comply with study visits or procedures. This history must include documentation of the subject's sickle cell disease, including dates of diagnosis and history of treatments, as well as all previous surgeries, immunizations and medications, with dates of diagnosis and treatment. A complete allergy history, including diagnosis and treatment, must also be documented.

#### 11.1.2. Vital Signs

Vital signs, including blood pressure, heart rate and oral body temperature ( $^{\circ}\text{C}$ ) will be measured at screening pre-run-in, immediately prior to dosing, at regular frequent intervals on day 0, and at each follow-up visit, as outlined below.

- On Day 0 every 15 minutes for 1 hour or until stable, then every 30 minutes post-infusion
- On days 7 and 14, and at monthly follow-up visits or at any unscheduled visit using the standardized process:
  - The subject should sit for five minutes with feet flat on the floor and his/her measurement arm supported so that the midpoint of the manometer cuff is at heart level
  - A mercury sphygmomanometer or automatic blood pressure device with an appropriately-sized cuff with the bladder centered over the brachial artery should be used
- Blood pressure and heart rate should be measured and recorded

Blood pressure should be recorded to the nearest 2 mm Hg mark on the manometer or to the nearest whole number on an automatic device.

#### 11.1.3. Weight

Weight (kg) will be measured at screening run-in. Subjects should be weighed wearing indoor, daytime clothing with no shoes. Before being weighed, subjects should empty their bladder.

#### **11.1.3.1. Physical Examination/Physical Assessment**

A physical examination directed toward subject medical history and current disease (consisting of head, eyes, ears, nose, throat, respiratory, gastrointestinal, extremities, musculoskeletal, cardiovascular, nervous system, lymph nodes, abdomen, dermatologic, and other physical conditions of note) will be performed at screening pre-run-in, prior to dosing at Day 0, and at the EOS visit (Table 3).

A physical assessment is a physical exam performed by someone other than the Investigator or sub-Investigator (this may be a Registered Nurse or Physician's Assistant), the purpose of which is to determine general physical health of the subject and any changes from prior visits. All other physical examinations will be symptom-based or system-directed to evaluate adverse events or subject status. Physical assessments will be performed 6 hours after the infusion, on days 7 and 14 and monthly until EOS visit.

#### **11.1.4. Electrocardiogram (ECG)**

A 12-lead ECG will be performed at screening run-in and at the EOS visit, after the subject has been in the supine position for at least 10 minutes. The ECG will include all 12 standard leads and will be recorded at a paper speed of 25 mm/sec. Standard ECG parameters will be measured, including RR, PR, QTc interval, and QRS duration. All ECGs must be evaluated by a qualified physician for the presence of abnormalities.

#### **11.1.5. Laboratory Assessments**

Unexpected abnormal laboratory results will be defined as AEs and graded per CTCAE v. 4.03 criteria. All abnormal laboratory values will be reviewed by the investigator, who will determine clinical significance and relationship to NKTT120. Significantly out-of-range values will be flagged for rapid review by the investigator.

